
***Analysis***

Descriptive analyses will be performed for all data, as well as graphic representations of the changes in monthly rates for each indicator aggregated to the level of each of the four selected UFMGs. Given the hierarchical nature of the data (repeated measures nested at the patient [indicator 3] or professional [indicators 1 and 2] level, which in turn are nested within the UFMGs), we will use multilevel analyses. These models will be adjusted to examine the effects of the various factors and of the implementation levels of advanced access on each of the three indicators. This type of model allows us to take into account the correlation between repeated measures for a single individual (patient or professional) over the study period, as well as missing data and patients lost to follow-up [52]. For the 4th indicator, trends will be analyzed using *join point* regression analyses [53]. This technique will be used to compare attendance rates among the 47 UFMGs and detect whether there have been significant changes in the direction or size of the linear trends for the rates over the 12 months of the study.

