### Study objectives

The primary objective of this study is to assess the variation in the implementation of the five guiding principles of advanced access in UFMGs across Quebec and to better understand the influence of the contextual factors on this variation and also on outcomes. The specific research objectives are to:
Measure the variability in the implementation of the five guiding principles of advanced access across all UFMGs in Quebec and identify the contextual factors influencing the implementation of advanced access;Gain a deeper understanding of how the contextual, organizational and professional factors influence the implementation of advanced access in four UFMGs;Compare the outcome indicators of advanced access in four UFMGs with regards to its implementation levels (e.g. average wait time for the third appointment, average rate of missed appointments, relational continuity of the team, attendance rate at the UFMG).

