##### Analysis

To respond to *objective 1* (assess the implementation of the five guiding principles of advanced access in the UFMGs), a score will be calculated for each principle, by type of respondent. Implementation scores will be assessed for each advanced access guiding principle by type of professional. Then, scores will be aggregated to produce group scores at the UFMG level for each of the above-mentioned principles. The median or average of all UFMGs’ score will be used as a threshold to determine the implementation categorization (e.g., strong/weak) of the advanced access for each principle. Descriptive analyses in terms of proportions, means, or standard deviations will be generated to determine the implementation scores of each principle and the factors influencing implementation. Multiple linear and logistic regression analyses will be performed using SAS 9.4 to determine the influence of different factors on implementation scores.

The Phase 1 results will be used to produce an implementation profile (e.g., strong/weak) of the UFMGs to guide the selection of the four cases which will be further analyzed in depth in Step 2.

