#### Step 2: Multiple contrasted case study based on mixed data

##### **A)** Qualitative component

***Data collection***

We will select four contrasted cases representing implementation profiles (*n* = 2 cases with high score, n = 2 cases with low score) and various geographical contexts and organizational size of UFMG (n = 2 cases in urban areas, n = 2 cases in rural/semi-rural areas). Previous studies have shown that context have a major influence on the types of collaborative practices among professionals [41].

For each UFMG in the study (*n* = 4), we will first perform a documentary analysis (e.g., algorithm of the patient’s path through advanced access, operating rules for team members). Then, a researcher and the research coordinator will conduct and record semi-structured interviews (60 min; at the UMFG) to reach data saturation (*n* = 11 interviews/case: two physicians, two PCNPs, two nurse clinicians, the physician in charge, one manager, two administrative assistants, one continuous quality improvement officer). The professionals will be recruited by email using purposive and snowball sampling strategies addressing first the medical director [42].

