##### B) Quantitative component

***Data collection***

Impact analyses will be conducted in the four selected UFMGs. We will use data retrieved from the electronic medical records (EMR) for the three first indicators presented below and data from the MHSS data bank for the fourth indicator. All UFMGs in Quebec have a functional EMR system. Because the UFMGs are attached to health facilities, we will be able to obtain all the EMR data for research purposes with the authorization of the directors of professional and hospital services without needing explicit consent from patients. On average, there are 20 physicians, 18 residents, two nurse clinicians, and one primary care nurse practitioner working in each UFMG, with an average of 5112 patients registered [45]. Thus, we calculated the estimated numbers in our samples as follows: around 160 professionals and 20,000 patients. The four indicators will be measured monthly over a one-year period.

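### Objective 3 models the effect of implementation level on indicators 1 to 3, but that effect rests on four clinics (2 high, 2 low) and supports only a descriptive contrast

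*Protocol article*

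**What the plan says.** Under Study objectives, the third specific objective is to "Compare the outcome indicators of advanced access in four UFMGs with regards to its implementation levels".

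Implementation level is defined in the Step 1 Analysis section. Each guiding principle is scored by type of professional. "Then, scores will be aggregated to produce group scores at the UFMG level for each of the above-mentioned principles", and the median or mean across UFMGs is the cut-off for categories such as strong and weak.

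Step 2, A) Qualitative component, Data collection, selects four contrasted UFMGs by implementation profile ("2 cases with high score, n = 2 cases with low score") and by setting ("n = 2 cases in urban areas, n = 2 cases in rural/semi-rural areas"), with organizational size also considered.

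Step 2, B) Quantitative component, Data collection, states: "Impact analyses will be conducted in the four selected UFMGs". It describes the sample as "around 160 professionals and 20,000 patients", with monthly measurement for one year.

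The Analysis section of the same component starts with descriptive summaries and graphs for each UFMG. It then specifies multilevel models, with repeated measures within patient or professional and these within UFMG, to "examine the effects of the various factors and of the implementation levels of advanced access on each of the three indicators". Indicator 4 is handled separately, by join point regression across 47 UFMGs.

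**The concern.** Implementation level, as used to choose the cases and to frame objective 3, belongs to the clinic. Everyone in a given UFMG shares the same value. More patients, professionals or months sharpen the estimate for each clinic but do not replicate the exposure, which occurs twice at each level.

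Two consequences follow. First, the sample that bears on the implementation effect is four, while the article describes it by its professionals and patients. Second, any two high clinics differ from any two low clinics in many other respects (setting, size, staffing, patients), and four clinics give almost no room to adjust for these. Ordinary variation between four clinics could then be read as an effect of implementation. The integration and dissemination sections carry these results into recommendations for decision-makers, and the Discussion expects to identify which principle, or which combination, is critical.

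**Working it through.** **Inputs from the protocol article**
- Clinics in the impact analysis: 4, as 2 high and 2 low.
- Staff: "On average, there are 20 physicians, 18 residents, two nurse clinicians, and one primary care nurse practitioner working in each UFMG", so 20 + 18 + 2 + 1 = 41 professionals per UFMG.
- Registered patients per UFMG: 5112 on average.
- No alpha, ICC, power or degrees-of-freedom method is given for these models.

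**Assumptions:** two-sided 5% level; clinic ICC 0.01 to 0.20; one averaged value per person, so the 12 monthly measures are not modelled separately.

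**1. The plan's own sample figure.** 4 × 41 = 164 and 4 × 5112 = 20,448. Both agree with the stated 160 and 20,000.

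**2. Degrees of freedom.** For a clinic-level contrast, df = clinics − clinic-level parameters = 4 − 2 (intercept, implementation) = 2. Each further clinic-level term costs one more. Two-sided 5% critical values are 4.30 on 2 df and 12.71 on 1 df, against 1.96 for a normal test. A permutation check agrees: there are 6 ways to split four clinics 2 versus 2, so the smallest two-sided p-value is 2/6 = 0.33.

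**3. Effective sample size.** With m people per clinic, effective N = 4m / [1 + (m − 1) × ICC], which cannot exceed 4/ICC. For patients at ICC 0.05: 20,448 / 256.55 = 79.7, against a cap of 4/0.05 = 80. Across ICC 0.01 to 0.20 the cap runs from 400 down to 20.

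**4. Type I error with a normal or large-df test.** When between-clinic variance dominates, the statistic follows t on 2 df, and P(|t| > 1.96) = 0.189. Simulation of a balanced clinic-random-intercept model under no effect (REML variance truncated at zero, 400,000 runs, 2 versus 2 clinics):

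| Assumed ICC | Patients (5112 per clinic) | Professionals (41 per clinic) |
|---|---|---|
| 0.01 | 0.19 | 0.07 |
| 0.05 | 0.19 | 0.13 |
| 0.10 | 0.19 | 0.16 |
| 0.20 | 0.19 | 0.18 |

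The rate is lower for professionals because the clinic variance is often estimated as zero with 41 per clinic.

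**5. The same model with t on 2 df.** Rejection under no effect is at most 0.05, so the test is valid. For power, the high-low difference has variance v/2 + v/2 = v, where v is the variance of a clinic mean, so the noncentrality is the difference in SDs of clinic means. Power by noncentral t is 0.10, 0.22 and 0.39 at 1, 2 and 3 SD. It reaches 80% at about 5.7 SD.

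**The case against.** The best defence is that this is a multiple case study reported in a condensed article. The objective says only compare, descriptive summaries per UFMG come first, and the integration section feeds the indicators into case matrices. That stands, and it means much of the descriptive remedy is already planned. It does not cover the models: they are listed separately from the descriptive work, are said to examine effects, and are nowhere labelled exploratory. The number of clinics is fixed, and no later analysis plan can add to it.

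Several stronger readings are tempting but unsupported:

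- **That the p-values will be invalid.** For indicators 1 to 3 the article names no test or df method, and an analysis plan may supply one. The inflation in step 4 is conditional on a normal or large-df test.
- **That the clinic level will be ignored.** This would give far larger error rates, but the Analysis section states that individuals are nested within UFMGs.
- **That implementation and geography are crossed, one clinic per cell, leaving 1 or 0 df.** Only marginal counts are given, and geography and size appear as selection criteria, not as model terms. If both high clinics shared a setting, the two factors could not be separated at all.
- **That every effect in the planned models is limited to four units.** Some professional factors in the conceptual framework can vary within a clinic.

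Scores by type of professional also make a within-clinic exposure conceivable for indicators 1 and 2. However, objective 3 and the case selection define implementation level by UFMG, and that is the more natural reading.

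**Conclusion.** The point holds in this form: the planned effect of implementation level on indicators 1 to 3 rests on four clinics, with at most 2 df, and cannot be distinguished from other differences between those clinics. The choice of test decides only how the analysis falls short. A normal or large-df test has type I error of about 19% (patients) or 7 to 18% (professionals). A t test on 2 df keeps its level but needs about 5.7 SDs of clinic means for 80% power.

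The df count follows from the document. The error rates depend on the assumed ICC, the balanced model and one averaged value per person. Objective 1 and the planned join point analysis of indicator 4 are unaffected.

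**What to change.** In Step 2, B) Quantitative component, Analysis:

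- Enter UFMG as a fixed effect, keep random effects for patient or professional, and report four clinic-specific estimates with confidence intervals for each of indicators 1 to 3. A separate implementation term is then redundant, because it is a combination of the clinic effects.
- Present high versus low, and any other clinic-level factor, as descriptive or exploratory, without p-values. Effects of factors that vary within clinics may still be modelled.
- Reword objective 3 as a descriptive comparison of four contrasted cases, and say beside the sample figures that the implementation contrast has four units.

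Optionally, add an analysis relating indicator 4, which the ministry holds for all UFMGs, to the Phase 1 implementation scores. This is new work beyond the join point regression and is limited to UFMGs that respond to the survey (about 80% of directors are expected to reply).

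The core change needs no new data, only a revised model and wording. Its cost is giving up inferential claims about implementation level on indicators 1 to 3.

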*The average wait for the third available appointment.* This is the most accurate indicator for measuring the impact of advanced access implementation [37, 46]. It is used to assess the time required for an appointment and refers to the number of business days before the third available appointment in a professional’s schedule, for a regular or follow-up appointment [47]. It reflects availability more accurately than using the first or second available appointment, as these could result from a recent cancellation or an unanticipated event [13, 27]. As suggested by several authors, including the *Quality Improvement Guide* [48], Pickin et al. (2004) [27], and Jones et al. (2003) [49], we will calculate, every Tuesday, the median number of days until the third available appointment, and then the monthly average for each professional in the UFMGs [27].*Average rate of missed appointments (no-shows).* An underlying premises of advanced access is that providing a system of timely appointments leads to greater efficiency, with fewer missed (no-show) appointments [37]. Several studies have shown positive impacts on this indicator [50]. No-shows are defined as appointments that are scheduled but not used, excluding those cancelled or changed by the professional, and that are registered by the administrative staff in the EMR. We will calculate on a monthly basis, for each professional, the number of no-shows in relation to the total number of scheduled appointments [51]*.**Relational continuity.* Relational continuity is an important feature of primary care quality [48]. Patients followed by a professional whom they trust generate fewer visits [48]. While new organizational models rely on patients being managed by a team of professionals, advanced access aims first to optimize appointments with the professional to whom the patient is affiliated, depending on the need for the visit and the professional’s availability. Relational continuity is calculated as the number of visits with the physician and other team partner (e.g., nurses, residents) responsible for that patient’s follow-up care divided by the total number of that patient’s visits at the clinic [37*,*^48^]*. T*his indicator can be broken down into two complementary measures: 1) the number of visits the patient had with his/her affiliated physician divided by total number of visits to the UFMG; and 2) the number of visits with other team partner following that patient (e.g., nurses, residents) divided by the total number of visits to the UFMG. Relational continuity with the team will be obtained on a monthly basis for each patient from the sum of these two measures.*Organizational continuity measures*. The aim of advanced access is that patients will consult the primary care clinic to which they are affiliated to satisfy the majority of their needs. Organizational continuity measures the proportion of primary-care medical services patients receive at their UFMG where they are attached. This is measured by the number of consultations at the UFMG divided by the total number of primary care consultations (including visits both to the UFMG and to the emergency room for less urgent cases). Monthly measures of attendance rates of UFMG patients will be obtained from the MHSS, a partner in this study, which holds accurate measurement data of this indicator for all FMGs and UFMGs since January 2016.

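### Indicator 4 gets a joinpoint analysis on 12 monthly points, too short to separate season from a change in trend, and no stated model relates it to implementation level

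*Protocol article*

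**What the plan says.** - **Length of series.** Step 2, B) Quantitative component, Data collection: "The four indicators will be measured monthly over a one-year period". The same paragraph places the impact analyses in the four selected UFMGs.
- **Method.** Step 2, B), Analysis: "For the 4th indicator, trends will be analyzed using" joinpoint regression. The next sentence gives the purpose, to "compare attendance rates among the 47 UFMGs and detect whether there have been significant changes in the direction or size of the linear trends", and ties the detection of changes to "linear trends for the rates over the 12 months of the study". No seasonal term is named.
- **Implementation.** In the same section, the multilevel models examine the effects of various factors and of the "implementation levels of advanced access on each of the three indicators", meaning indicators 1 to 3.
- **Objective.** Study objectives, third objective: "Compare the outcome indicators of advanced access in four UFMGs with regards to its implementation levels". Its list of example indicators includes the attendance rate at the UFMG.
- **Available data.** The description of indicator 4 says the ministry (MHSS), a study partner, "holds accurate measurement data of this indicator for all FMGs and UFMGs since January 2016".

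**The concern.** Twelve months is a single seasonal cycle. The Background itself names flu season as a source of increased demand. If the attendance rate moves with the season, the series bends within the year, and a piecewise-linear fit without a seasonal term can take that bend for a change in trend. The plan would then call it significant.

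The second issue is the link to objective 3. Attendance is one of the outcomes to be compared by implementation level, yet the only inferential method given for it contains no implementation term. It is also the one indicator that the plan analyses in all 47 UFMGs, and Phase 1 is to produce implementation scores at UFMG level. What is at stake is one of the four outcome indicators: its headline result could be a seasonal artefact, and it would carry no modelled information on implementation.

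**Working it through.** **The plan's own figure.** Monthly measurement for one year gives 12 points per UFMG, which agrees with the 12 months in the Analysis section. No alpha, effect size or variance is stated for indicator 4, so there is nothing else to reproduce.

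**Step 1: degrees of freedom (no assumption about size).** Intercept plus 11 month terms has rank 12, so with 12 points the residual df are 12 − 12 = 0. The linear trend and any joinpoint already lie in the space spanned by the month terms and cannot be estimated beside them in a single series. With an assumed 48 months, month terms plus trend have rank 13. One joinpoint makes 14, leaving 48 − 14 = 34 df.

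**Step 2: simulation.** Assumptions, none of them from the article: alpha 0.05; independent normal errors with SD 1; one continuous joinpoint at least two points from either end, tested against a simulated 5% critical value; a sinusoidal season with random phase.

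12 points, no seasonal term, no true change in trend:

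| Seasonal amplitude (residual SD) | Joinpoint declared |
|---|---|
| 0 | 5% |
| 0.5 | 11% |
| 1 | 29% |
| 2 | 66% |
| 3 | 78% to 80% over repeat runs |

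12 points, no season, true slope change at mid-year:

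| Change (SD per month) | Power |
|---|---|
| 0.25 | 0.09 |
| 0.5 | 0.21 |
| 1 | 0.64 |
| 2 | 1.00 |

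**Step 3: does a simpler seasonal term rescue 12 points?** One annual sine and cosine pair brings the false-joinpoint rate back to about 5%. However, it inflates the variance of a mid-year slope change about 101-fold, and power falls to about 5% at every size tried (0.25 to 2 SD per month).

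**Step 4: the longer series.** The pretest was in spring 2019. January 2016 to March 2019 is 3 × 12 + 3 = 39 months, so with 12 study months at least about 39 + 12 = 51 are available. Simulated at 48 and 60 months, with a change of 0.5 SD per month six months before the end:

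| Length | Seasonal term | False joinpoints | Power |
|---|---|---|---|
| 48 | harmonic | about 5% | 0.78 |
| 48 | month terms | about 5% | 0.75 |
| 60 | harmonic | about 5% | 0.82 |
| 60 | month terms | about 5% | 0.81 |

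**Step 5: implementation.** Objective 3 lists attendance among the outcomes to compare by implementation level. The models with implementation level cover three indicators, and the fourth is handed to joinpoint regression. No stated statistical model makes the comparison for attendance.

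**The case against.** The strongest reply has four parts.

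*The indicator is not unrelated to implementation.* This stands. Objective 3 states the intent, the Analysis section plans graphs of each indicator for four UFMGs chosen as two high and two low scorers, and the integration section carries the objective 3 impact variables into case matrices. A reader might infer that attendance is never related to implementation; only a statistical model is absent.

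*The seasonal size is undocumented.* This stands. Indicator 4 is a ratio of UFMG consultations to UFMG plus less urgent emergency visits. Extra demand may raise both parts, and the article gives no seasonal movement in the ratio. The rates in Step 2 are illustrative, and spurious findings are possible, not certain. The df count in Step 1 does not depend on this.

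*A season shared by all UFMGs cancels in a comparison between them.* This is partly right. It does not help the stated aim of detecting changes in the trends themselves, nor does it remove seasons that differ between UFMGs.

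*Objective 3 concerns four UFMGs.* This is correct, so an analysis of implementation across all UFMGs extends the objective. It is tempting to say that the plan throws away its only well-replicated test. With 38 to 47 UFMGs (0.80 × 47 = 37.6), Fisher-z power for a correlation of 0.4 would be 0.71 to 0.80, but 0.4 is an arbitrary value and limiting the objective to four cases is a design choice.

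Two further inferences also go too far. One might count 47 × 0.05 = 2.35 expected false positives and a 1 − 0.95^47 = 0.91 chance of at least one, but the article does not say that 47 separate independent tests are planned. Nor are the earlier data already with the investigators: the partner holds them and they must be obtained.

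**Conclusion.** The concern holds in two limited respects.

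First, a 12-month joinpoint analysis cannot separate season from a change in trend. For calendar-month terms within a series this is a matter of counting: 12 parameters and 12 points. The size of the resulting error is not known. Under the stated assumptions it ranges from 5% with no season to about 80% at an amplitude of 3 residual SD, with about 21% power for a real mid-year change of 0.5 SD per month.

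Second, no stated statistical model relates attendance to implementation level, although objective 3 lists it; what is planned is descriptive and confined to the four cases.

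Both follow from what the article fixes, namely the 12-month window and the restriction of the implementation models to three indicators. They are not details it merely leaves to a fuller plan. The scope of four UFMGs in Data collection and 47 in Analysis also needs to be reconciled. The matter is worth correcting because the correction is cheap. It touches one of four indicators and does not undermine the study.

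**What to change.** 1. Obtain from the MHSS the monthly indicator 4 series for all UFMGs from January 2016 through the study year.
2. Fit one mixed model across UFMGs with calendar-month terms, a linear trend, and a random intercept and slope for each UFMG. Keep 12-month joinpoints as a descriptive display, without significance claims.
3. Add the Phase 1 UFMG implementation score, with its effect estimated for the study year only. Earlier years serve to estimate season and prior trend. A score measured after the spring 2019 pretest should not be applied to outcomes back to 2016, because that puts exposure after outcome.
4. Report the score effect as a supporting association across the UFMGs that have scores, beside the four-case comparison, and describe it as an extension of objective 3.
5. State in Data collection and in Analysis which indicators are analysed in four UFMGs and which in 47.

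**Cost:** a longer extract from a partner already supplying the indicator, and revised analysis wording. Implementation levels before the survey remain unknown, so the longer series improves the handling of season and trend but adds little to the implementation contrast itself.
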